# Efficacy of mHealth and education-led peer counseling for patients with hypertension and coronary artery disease in Pakistan: study protocol for a double-blinded pragmatic randomized-controlled trial with factorial design

**DOI:** 10.1186/s13063-023-07472-0

**Published:** 2023-07-10

**Keywords:** Mobile health, eHealth, Intervention, Medication adherence, Hypertension, Systolic blood pressure

## Abstract

**Background:**

Hypertension is a highly relevant public health challenge. Digital interventions may support improving adherence to anti-hypertensive medications and alter health behavior. Therefore, this protocol describes a study that aims to assess the effectiveness of mHealth and educational support through peer counseling (Ed-counselling) to control blood pressure in hypertensive patients when compared to standard care.

**Methods:**

We chose a double-blinded pragmatic randomized-controlled with factorial design for this investigation. The trial is going to recruit 1648 hypertensive patients with coronary artery disease at the age of 21 to 70 years. All participants will already be on anti-hypertensive medication and own a smartphone. They will be randomized into four groups with each having 412 participants. The first group will only receive standard care; while the second group, in addition to standard care, will receive monthly Ed-counselling (educational booklets with animated infographics and peer counseling); the third group will receive daily written and voice reminders and an education-led video once weekly together with standard care; while the fourth one gets both interventions given to second and third groups respectively. All groups will be followed-up for 1 year (0, 6, and 12 months). The primary outcome will be the change in systolic blood pressure while secondary outcomes include health-related quality of life and changes in medication adherence. For measuring changes in systolic blood pressure (SBP) and adherence scores difference at 0, 6, and 12 months between and within the group, parametric (ANOVA/repeated measure ANOVA) and non-parametric tests *(*Kruskal*-*Wallis test*/*Friedman test*)* will be used. By using the general estimating equation (GEE) with negative binomial regression, at 12 months, the covariates affecting primary and secondary outcomes will be determined and controlled. The analysis will be intention-to-treat. All the outcomes will be analyzed at 0, 6, and 12 months; however, the final analysis will be at 12 months from baseline.

**Discussion:**

Besides adding up to existing evidence in the literature on the subject, our designed modules using mHealth technology can help in reducing hypertension-related morbidity and mortality in developing countries.

**Supplementary Information:**

The online version contains supplementary material available at 10.1186/s13063-023-07472-0.

## Background

Hypertension among adults is an increasing public health challenge that affects 1.13 billion people around the globe [1] and is considered a major cause of mortality resulting in 9.4 million deaths worldwide per year [2]. About 75% of all hypertension cases are diagnosed in low-and middle-income countries (LMICs) [1, 3]. The risk of cardiovascular events can be reduced to about one-half for every 20 mmHg decrease in systolic blood pressure and 10 mmHg in diastolic blood pressure [4]. Likewise, cardiovascular disease-related deaths are preventable and can be better managed by reducing systolic blood pressure [5].

In Pakistan, 18.9% of teenagers over the age of 15 years and 33% of adults over the age of 45 years suffer from hypertension [6]. Adherence is termed as “the extent to which individuals follow their healthcare providers’ prescribed drug schedules” [7]. Adherence to cardiac medications was reported at 77% [8], while non-adherence to antihypertensive medication was found among 37.7% of patients in Pakistan [9]. Thus, non-adherent patients constitute a significant proportion of the treatment population in the country. Also, the majority of individuals on antihypertensive medications had uncontrolled blood pressure and poor adherence to treatment which further compounds the dysregulation of an individual’s blood pressure [9, 10].mHealth is a term used for any medical and public health application supported by mobile phones, personal digital assistants, patient monitoring devices, or other wireless devices [11]. The use of mobile health interventions to enhance medication adherence has been reported to be effective, particularly in LMICs [12–14] as these provide results at a lowered cost [15]. Despite positive feedback reported on the effectiveness of mHealth interventions on adherence to medication in general, its role in cardiovascular medication adherence is under-studied especially in a scarcely resourced country like Pakistan. Moreover, in the context of behavior changes in response to the changing dynamics of disease, there is a need to compare mHealth intervention with different interventional methods to assess its effectiveness [16]. Similarly, the literature suggests that counseling therapy is also an effective strategy in modifying behavior regarding adherence to antiretroviral and anti-tuberculosis treatment [17–19]. Counseling was found to be an affordable intervention at the personal level in enhancing medication adherence [20] but its use in hypertension and cardiovascular diseases is limited.

There is a need for an efficient and cost-effective model to be adopted in LMICs like Pakistan, where there is a lack of resources (e.g., constraints on the public health budget) and where people have a generally poor educational status. Most of the interventions in improving medication adherence are not financially affordable besides having complex designs. It is therefore imperative to work on improving adherence to anti-hypertensive medications and altering behavior by designing cost-effective interventions with lesser intricacies.

This study is based on the experiences of a previous study that has been conducted as a doctoral thesis by the first author. We are going to investigate the effectiveness of two modules that are designed for this study. The first module is Ed-counselling and the second one is a mHealth intervention in altering beliefs regarding adherence to treatment and lowering systolic blood pressure in hypertensive patients with coronary artery diseases. This research will compare these two models to know which one is more accepted and effective in the Pakistani population. This study is expected to yield substantial findings and may aid in the development of educational guidelines for patients to increase drug adherence and reduce untoward consequences.

### Research objectives

To determine the mean differences in treatment outcome (systolic blood pressure) among the four groups at 0, 6, and 12 months after the interventionTo assess the effect of newly developed intervention modules on health beliefs related to treatment outcome (systolic blood pressure change) among patients with hypertension on anti-hypertensive treatmentTo determine the mean differences in (medication) adherence among the four groups at 0, 6, and 12 months after the interventionTo measure the health-related quality of life at 0, 6, and 12 months after the intervention

## Methods

### Study design

It is a factorial randomized controlled trial with a superiority design and a double-blinding approach. Intention-to-treat analysis with 12 months of follow-up will be applied to determine the efficacy of Ed-counselling assistance and mHealth intervention on hypertensive patients at four teaching hospitals in Lahore, Pakistan. Lahore is the provincial capital of Punjab (the largest province in the country) [21]. It is the world’s eighteenth-largest city and Pakistan’s second-largest metropolis. The SPIRIT 2013 Statement (Standard Protocol Items: Recommendations for Interventional Trials) [22] provides the basis for this research. A factorial approach will be used to assign participants to the four groups. The groups will receive standard care, Ed-counselling, mHealth intervention, and combined intervention (Fig. 1). All groups will be followed up for a period of total 12 months. Systolic blood pressure, the Self-efficacy for Appropriate Medication Adherence Scale (SEAMS), the number of prescribed tablets taken for a specified period (self-reporting), and health-related quality of life will be measured at least three times: at baseline, 6 months, and 12 months after the intervention [23, 24].

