### Randomization and blinding

To avoid any potential bias, a simple complete randomization procedure will be utilized [26]. A computer-generated, simple complete random approach will be used to divide participants into four groups [27]. To keep their identities hidden, all participants will be assigned an identification number. To keep the allocation of participants into four groups hidden from the research staff, tight concealment of allocation will be observed. Before allotment, written assignments will be sealed in opaque packets with tagged identifying numbers [28].

All subsequent randomization processes will be completed by an independent biostatistician who will no longer be a participant in the trial. Independent personnel will be involved in the randomization, evaluation, and intervention delivery. The staff involved in data collection and outcome assessment will be blinded. They will be unaware of the allocation of any group [29].

The recruitment process will continue until a final sample size of 1648 people from four teaching hospitals is reached. Participants’ follow-up period is 12 months from the point of randomization (Fig. 2).

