	**mHealth intervention**	

The first group will receive no intervention and only standard hospital care (as per the practice of the hospital); the second group will receive monthly Ed-counselling sessions in addition to standard care; the third group will receive daily written and voice reminders and once weekly an education-led video in addition to standard care; the fourth group will receive Ed-counselling sessions every month, daily written and voice reminders, and once weekly an education-led video in addition to standard care.

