We will assess self-reported information regarding the number of tablets that will be utilized by participants within the specified timeline divided by the number of pills prescribed for that time multiplied by a hundred for the last 7 days. A rate of ≥ 80% will be considered adherent and vice versa [7, 8]; thereby, the percentage of participants who are successful in achieving adherent status between baseline and 12 months will be evaluated. In addition, to measure the adherence score at baseline, 6 months, and 12 months post-intervention, an Urdu/English version of the “Self-efficacy for Appropriate Medication Adherence Scale” (SEAMS) will be employed [33, 34]. The SEAMS is a 13-item measure for evaluating medication self-efficacy in chronic disease management that looks to be appropriate for people with low literacy abilities [34]. This survey will use a three-point response system, with 1 indicating lack of confidence, 2 indicating moderate confidence, and 3 indicating extreme confidence. The 13-item scale had a range of possible scores from 13 to 39. High scores indicate better adherence.

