### Data management

Two trained research assistants will gather data under the supervision of a research specialist. In sealed envelopes, all collected data will be delivered to a bio-statistician who will not be involved in any of the research activities and will be unaware of each participant’s assignment. All data must be entered twice, according to institutional regulation. The bio-statistician will clean and analyze the data. Stata version 16 (Stata corp SE) and R (version 4.0.3) will be utilized for all kinds of analysis in this study.

The research staff involved in data collection will include two research assistants and one research specialist. Two research assistants, in partnership with local hospital staff and under the supervision of a research specialist, will collect the data. A 2-day on-site training of research assistants on hypertension and its control, treatment, and how to respond to common questions about blood pressure and medication adherence including medication side effects will be conducted using a standard training module developed by a team of specialists from one of the study hospitals. They will also provide counseling and support to participants in filling out surveys. Data collection and randomized controlled trial procedure guidelines will be covered in three training sessions.

Each participant will receive a 5-min personal consultation to assist them in filling out the questionnaire, measuring their blood pressure, and counting their pills. Systolic blood pressure will be recorded by a nurse who will be oblivious to the study participants’ group. MODEL-605P YAMASU, a calibrated upper-arm mercury sphygmomanometer, will be utilized for this purpose. The blood pressure of the participant will be measured according to conventional procedures. Within 5 min, two different readings will be collected, with the average measurement being the final measurement. If the difference between the two measures is greater than 5 mmHg, a third evaluation will be performed, with the average of the two closest measurements being used as the final measurement.

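### The trial is labelled double-blinded, but nothing in the protocol masks participants, so its self-reported secondary outcomes are unblinded

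*Protocol article*

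**What the plan says.** The title and abstract call the trial double-blinded, and Study design repeats it: "It is a factorial randomized controlled trial with a superiority design and a double-blinding approach".

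The protocol names these people as blinded:

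- Randomization and blinding: "The staff involved in data collection and outcome assessment will be blinded".
- Outcome measures and Data management: the nurse who records systolic pressure does not know the group.
- Data management: the biostatistician who cleans and analyses the data "will be unaware of each participant’s assignment".

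Roles are also separated: "Independent personnel will be involved in the randomization, evaluation, and intervention delivery".

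The arms are set out in the Intervention section. For control, "The first group will receive no intervention and only standard hospital care". For mHealth, "the third group will receive daily written and voice reminders and once weekly an education-led video in addition to standard care". The Ed-counselling arm has in-person sessions of 20 to 25 minutes, attended with a companion, and the fourth arm gets both interventions.

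The adherence and quality-of-life outcomes come from the participant. On the pill count, "We will assess self-reported information regarding the number of tablets that will be utilized by participants". SEAMS, EQ-5D-3L and EQ-VAS are questionnaires or self-ratings.

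**The concern.** In a trial of counselling and phone messages against standard care, a participant can tell whether counselling sessions or daily messages are arriving. Masking the staff who record an answer does not mask the person who gives it. The label therefore claims a property that the described design does not have.

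This matters for specific results. Participants in the intervention arms are counselled on adherence, reminded daily to take their medicine, or both, and are then asked how many tablets they took and how confident they are about taking them. Ethical considerations itself expects some participants to feel embarrassed when reporting poor adherence. The last counselling session is also placed at month 12, when the final outcomes are collected. A difference on these scales could be a change in behaviour, a change in reporting, or both. A reader who trusts the label would not consider the second.

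**Working it through.** **1. Who is masked, by role**

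| Role | What the protocol supports |
|---|---|
| Participant | Not stated to be blinded; overt arms, no sham |
| Intervention deliverers (hypertension doctors, IT facilitator) | Not stated to be blinded; they know whom they treat or message |
| Data collectors and outcome assessors | Stated to be blinded |
| Nurse reading systolic pressure | Stated to be blinded |
| Biostatistician | Stated to be blinded |

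That participants know which intervention they receive is an inference from the arm descriptions, not a statement in the text, but it is a safe one. The free WhatsApp connection for all participants does not hide who gets messages.

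**2. Who supplies each outcome**

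- Systolic pressure, and the proportion at or below 140 mmHg: measured by the blinded nurse.
- 7-day pill count, SEAMS, EQ-5D-3L, EQ-VAS: reported by the participant.

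**3. The plan's own sample size, to fix the number per arm**

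Inputs (Sample size section): SD 18.5, means 148 and 143, two-sided 5%, power 90%, attrition 30%.

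- n = 2 × (1.960 + 1.282)² × 18.5² / 5² = 287.7, so 288 evaluable per arm.
- 288 / 0.70 = 411.4, so 412 per arm; 4 × 412 = 1648.

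The stated figure is reproduced. It concerns systolic pressure and does not depend on blinding.

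**4. Illustration for the adherence proportion**

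Inputs: non-adherence 37.7% (Background, a cited background figure and not a trial parameter), so adherence is 62.3%; 288 per arm. The over-reporting fractions are assumed. No true effect is assumed.

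SE of a difference between two arms = √(2 × 0.623 × 0.377 / 288) = 0.040.

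| Over-reporting among the non-adherent | Spurious difference | In SE |
|---|---|---|
| 1 in 10, intervention arm only | 0.377 × 0.10 = 3.8 points | 0.9 |
| 1 in 4, intervention arm only | 0.377 × 0.25 = 9.4 points | 2.3 |
| 1 in 4 intervention, 1 in 10 control | 0.377 × 0.15 = 5.7 points | 1.4 |

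The last row shows that only the difference in over-reporting between arms counts.

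**5. Chance of a false positive under assumed bias**

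One pairwise comparison, two-sided 5%, 288 per arm, no true effect, normal approximation:

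- Adherence proportion shifted by 5, 10 or 15 points: about 24%, 73% or 98%.
- A score shifted by b SD: Φ(b/√(2/288) − 1.96) + Φ(−b/√(2/288) − 1.96). For b = 0.1, 0.2, 0.3 this is about 22%, 67%, 95%.

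**6. The sentence on counselling by data collectors**

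Data management says of the research assistants: "They will also provide counseling and support to participants in filling out surveys". The next paragraph of that section gives every participant a five-minute consultation for the same purpose. The tested counselling is led by hypertension doctors, and delivery and evaluation have separate personnel. The natural reading is help with forms, in all arms.

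**7. Contact with the intervention groups only**

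The section on discontinuing or modifying interventions has a research-team member phone only the intervention groups at one month. Nothing says that this person is kept out of outcome assessment.

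**The case against.** The strongest reply is that this is a loose label and not a hidden procedure. Assessors and analyst are both masked, and the text says so, so a careful reader can see who is blinded. The primary outcome is read by a blinded nurse, the affected outcomes are already secondary, and self-report is inherent to SEAMS and EQ-VAS. The over-reporting fractions have no source in the document, and the smaller one stays below one standard error.

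Most of that stands, and it limits the point. It does not rescue the label. The term does not say which parties are masked, and the Unblinding section speaks of unblinded participants as if they had been blinded before.

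Three stronger readings are tempting and are not supported:

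- **That data collectors give control participants the tested counselling.** A reader might infer this from the word counseling in Data management and from the assistants' training on blood pressure and adherence questions. The sentence ties the counselling to completing surveys, and other staff deliver the module.
- **That the contrast on systolic pressure is diluted.** This depends on the first reading, and no passage shows it.
- **That only assessors can be blind.** The biostatistician is also stated to be blinded.

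The phone call to the intervention groups is better evidence of a risk to staff blinding than the survey sentence. It too shows only an unstated separation of roles, not a breach.

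**Conclusion.** The concern holds in a limited form. The double-blinded label is unsupported for participants and for those who deliver the interventions. The pill count, SEAMS, EQ-5D-3L and EQ-VAS are unblinded self-reports, and differences between arms on them are open to differential reporting bias. Primary systolic pressure, as planned, is protected by a blinded nurse.

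The size is illustrative only: 3.8 to 9.4 percentage points on the adherence proportion, or about 0.9 to 2.3 standard errors. It rests on 37.7% non-adherence applying to the trial population, 288 completers per arm, over-reporting by 1 in 10 to 1 in 4 of the non-adherent, and none in the control arm. Over-reporting among controls would shrink it. The label is wrong whatever the size; whether the bias could produce a significant result depends on the assumed rate.

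**What to change.** - In the title, abstract and Study design, replace double-blinded with outcome-assessor- and analyst-blinded. In Randomization and blinding, add that participants and intervention deliverers are not blinded.
- Align the Unblinding section, so that it refers to breaking the blind of assessors or analyst.
- State that SEAMS, the pill count, EQ-5D-3L and EQ-VAS are unblinded self-reports and will be interpreted as such.
- In Data management, reword the assistants' task as neutral help with completing forms.
- State that the team member who phones the intervention groups at one month takes no part in outcome assessment.

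The cost is wording, plus confirmation of two staff roles. Trial status puts the end of recruitment at April 2023, before the article appeared, so the two staff statements should describe what is actually done. If practice differed, report that; changing questionnaire help during follow-up could make later data differ from baseline. The sample size and primary analysis are untouched. The label becomes less favourable.

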**Fig. 1 Fig1:**
[figure not shown]
Factorial distribution of the groups in the trial: mHealth, Ed-counseling, and standard care

### Study participants and eligibility criteria

The study participants will be hypertensive patients with coronary artery disease as comorbidity registered in the Cardiology Outpatient Departments (OPDs) of four selected public teaching hospitals in Lahore, Pakistan.

Inclusion criteria include men and women over the age of 21 and up to 70 years, who have been registered for the last 30 days or more as hypertensive with comorbidity of coronary artery disease in the OPDs of the selected teaching hospitals in Lahore, Pakistan. These participants will be having stable coronary artery disease, are already on anti-hypertensive medication, are willing to sign a written informed consent form, possess a smartphone with access to the Internet, and are able to read Urdu/English.

Patients with a history of cancer who may need drug changes; with a blood pressure reading of more than 220/120 mmHg; with any biological condition that makes it difficult for them to read, write, communicate, or hear phone calls; with pregnancy and in lactation period; and who are enrolled in some other study will be excluded.

